# Effectiveness of PUSH notifications from a mobile app for improving the body composition of overweight or obese women: a protocol of a three-armed randomized controlled trial

**DOI:** 10.1186/s12911-020-1058-7

**Published:** 2020-02-24

**Keywords:** mHealth, Obesity, Weight management, Physical activity

## Abstract

**Background:**

The penetration level of mobile technology has grown exponentially and is part of our lifestyle, at all levels. The use of the smartphone has opened up a new horizon of possibilities in the treatment of health, not in vain, around 40% of existing applications are linked to the mHealth segment. Taking advantage of this circumstance to study new approaches in the treatment of obesity and prescription of physical activity is growing interest in the field of health. The primary outcome (obese adult women) will be assessed according to age, fitness status, weight, and body composition status. Data will be collected at enrollment and weekly during 6 months of intervention on dietary practices, physical activity, anthropometry, and body composition. Analysis of effect will be performed comparing the outcomes between intervention and control arms. The message delivery is in progress.

**Methods:**

A 3-arm clinical trial was established. A series of quantitative and qualitative measures were used to evaluate the effects of self-weighing and the establishment of objectives to be reached concerning the prescription of physical activity. At the end of this pilot study, a set of appropriate measures and procedures were identified and agreed upon to determine the effectiveness of messaging in the form of PUSH technology. The results were recorded and analyzed to begin a randomized controlled trial to evaluate the effectiveness of the proposed methodology.

**Conclusions:**

The study is anticipated to establish feasibility of using PUSH notifications to evaluate whether or not an intervention of 6 months, directed by a team formed by Dietician-Nutritionist and nursing professionals, by means of an application for Smartphone and a personal consultation, improves the body composition of adult women with a fat percentage equal to or higher than 30% at the beginning of the study.

**Trial registration:**

Clinical Trials ID: NCT03911583. First Submitted: April 9, 2019. Ethical oversight is provided by the Bioethical Committee of Córdoba University and registered in the platform clinicaltrials.gov. The results will be published in peer-reviewed journals and analysis data will be made public.

## Background

The use of mobile technology and its presence in our daily lives is increasing exponentially. It has been estimated that, in 2019, worldwide, there will be more than 2700 million Smartphone users, and around 1400 million Tablet owners [1]. Also, the technical improvements in mobile devices, including larger displays and a higher resolution, an increase in surfing speeds and the development of an infinity of applications (APP) with a multitude of new functions [2], has signified an authentic social and cultural revolution, reaching all society levels. As a result, the incorporation of mobile technology into our daily habits has triggered changes in the way that we live, in our work, or in how we communicate and relate to each other socially [3].

According to the Global System Mobile Association (GSMA), there are more devices connected to the network than people in the world. In 2017, 7422 million mobile connections were identified, whereas the world population census was of 7228 million [4]. Another relevant fact that helps to size up the magnitude of this technological tendency is that, in 2014, the number of accesses and browsing time in the web through mobile devices exceeded, for the first time, those made by office desk equipment [3, 5–7]. The future of technology and the mobile phone are considered to be on equal terms, making it very difficult to distinguish between one and the other. Thus, it is believed that, in a few years, we shall be able to dispense with the adjective “mobile” when speaking about technologies as they will all have this characteristic [3].

The term mHealth (mobile health) was used and defined for the first time in 2000 [8]. This concept was subsequently employed in the 2010 mHealth Summit of the Foundation for National Institutes of Health (FNIH) to refer to “*the provision of medical attention services through mobile communication devices*” [9] and nowadays this is globally understood as a medical and public health practice based on the use of mobile devices [10]. Since then, up to now, around 40% of the over 300,000 applications available in the different apps stores are related to health themes, with those focused on the monitoring and management of diseases standing out [11]. Different strategies, going from phone calls or sending information through the Short Message Service (SMS), up to the use of applications such as those for clinical decision-making support or telemedicine, have shown themselves to be effective in the communication between patients and health professionals; the change toward healthy lifestyles (giving up smoking or increasing physical exercise); in the improvement of illness management (in diabetes or asthma, for instance); and in the increase in adherence to the treatments [12–15].

One of the characteristics of mobile applications is the sending and receiving of messages through a system of notifications known as “PUSH,” that consists of requests appearing on the display of the Smartphone at a scheduled time, permitting them to be customizable both in their contents and at the time of sending them. Their principal difference from SMS lies in the fact that the latter are asynchronous, i.e., it is not expected or required for the recipient to answer a message. However, PUSH notifications are pro-active as they offer visual or aural alerts to inform the recipient of a message or event received and invite them to act on them [16]. On receiving the notification, the user can interact in different degrees, from merely reading it to answering it, thus permitting feedback. Also, there is evidence of the PUSH notifications being effective in communications between professionals [17].

SMSs have demonstrated that they are an excellent resource for delivering electronic reminders in practice and a very feasible platform, being useful in increasing adherence to treatment [18], preventing complications in non-communicable diseases [19], facilitating inter-professional communication [20], and helping in disease self-management [21]. PUSH notifications (defined as an event-based mechanism where remote servers “push”/CONVEY events to Smartphone client apps) [22] has recently appeared in mhealth, showing its potential for improving pervasive functionalities in mobile health apps, allowing the delivery of timely updates and customized reminders to users or patients. One of the essential functionalities is to offer alerts to inform the user about a received message and invite him/her to act, even without needing to be the app being used [23]. Although this strategy has proved to be effective in communication with professionals [17] and assessing patterns of health behaviors [24], there is scarce evidence of its effectiveness in interventions aimed at changing lifestyles.

Interventions that use mobile and portable technologies can be useful in improving healthy habits or reducing high levels of sedentary behavior [25, 26]. It has been demonstrated that certain functions implicit in the habitual use of Smartphones, like the exchanging of information, the possibility of carrying out self-monitoring with natural, intuitive record systems, the interaction between users, or the employment of gamification strategies, also have positive effects on the health status [27].

Besides, the users should feel that they are part of the technology, it is especially important to involve patients in active commitments, like self-assessment in certain behaviours, or making timely follow-ups [28]. These measures have been seen to be efficacious in improving health markers, for example, weight management, and blood pressure [29].

The objective of a large part of the health interventions based on the use of APPs has been to improve nutritional status through dietary advice and an increase in physical activity (PA) [30]. In this sense, it has become evident that an increase in PA implies benefits to health and reduces mortality from all causes, regardless of the body mass index (BMI) [31]. Also, there is ample evidence of the role of PA in weight loss programs in the long-term prevention of recovering weight loss [32]. In past years, systematic reviews have been done in order to establish associations between physical activity and weight loss in overweight or obese individuals [33, 34], demonstrating the existence of an inverse association between the physical activity carried out and the BMI.

In this study, we aim to investigate whether mHealth that included text messages via PUSH notifications containing advice for dietary and lifestyle modifications for six months would reduce the percentage of total body fat among overweight or obese women adults aged 25–64 years in a predominantly urban Southern Spain population. The study also aims to evaluate the effects of the mHealth intervention on body mass index, dietary practices, and physical activity. As an initial hypothesis, we considered that those subjects assigned to the group receiving the PUSH notifications would adhere to the dietary recommendations and physical activity proposed, thus achieving a more significant fat loss and a higher increase in muscle mass.

## Methods/design

### Study design

A controlled randomized three-armed clinical trial was conducted that includes a physical activity lasting six months in women following the same dietary prescription. The groups were differentiated based on whether or not they received Push notifications from a mobile application (Nutrición Sur version 15.0.0). Thus, the control group did not receive these notifications, whereas the women who received them constitute an experimental group. Additionally, inside each group, three different subgroups were randomly established with distinct degrees of physical activity (PA) intensity; these could be light (LPA), moderate (MPA), or intense (IPA).

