### Sample size calculation

The primary outcome variable was fat mass loss after six months, and the anticipated minimum difference in the average fat mass loss was 2%, with an expected SD not exceeding 3.5% [35]. The study was designed to have at least an 80% power and an alpha level set at 0.5, obtaining a sample size of 27 individuals for each group (total *N* = 54). A total of 90 women (45 for each group), was estimated, to mitigate the effect of possible dropouts during this trial.

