### Statistical analysis

The quantitative variables were presented with the mean and the standard deviation, whereas the qualitative ones in frequencies and percentages. To contrast, the goodness of fit to a normal distribution of data from quantitative variables, the Kolmogorov-Smirnov test with the Lilliefors correction was used. For the bivariant hypothesis contrast, the two-means Student-t test was made, while, for the qualitative variables, the Chi-test and Fisher’s exact test was performed when necessary. Likewise, for the three or more means analysis, the ANOVA repeated means test was used to evaluate the effects of the intervention at the baseline moment, at 3 and 6 months, and the correlation between the quantitative variables was verified by Pearson’s (r) correlation coefficient. The ANCOVA analysis of covariance was applied to determine the effect of the baseline data on the modification of body composition. Finally, in the case of not fulfilling the criterion of normality or homoscedasticity, the non-parametric versions of the tests mentioned were conducted. Adjusted linear regressions were made for each variable of the body composition (%BF and MM) and the weight at the final moment of the study to estimate the standardized Beta coefficients possessed by the PUSH notifications in the achievement of objectives. For all the statistical analyses, an alpha error probability of under 5% (*p* < 0.05) was accepted, and the confidence interval calculated with a 95% security. For the statistical analysis, the computer program IBM SPSS Statistics version 22.0 will be used.

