## Discussion

The general objective of this protocol was to evaluate (1) the efficacy of PUSH notifications in an intervention aimed at improving the body composition of adult women who are overweight or obese, through dietary intervention, (2) analyzed the evolution of body composition based on PUSH notifications and prescribed physical activity. The intervention was evaluated through a randomized three-armed clinical test. It has been seen in the literature that the results of actions using mobile messaging via Push notifications could improve the degree of adherence to dietary prescriptions and physical activity, with different results. A significant number of women present physical activity levels below the minimum threshold recommend by official organizations. This sedentary lifestyle causes gains in total body weight and body fat. If the results of the assay demonstrate a positive effect, a new approach will be established based on the interaction of an APP and personal consultation, helping health professionals to establish real objectives in the prescription of physical activity and its follow-up in the patients who carry them out.

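### The randomisation described is a 2 × 3 factorial with six cells, yet the trial is called three-armed and no listed analysis names activity level, so the joint PUSH-and-activity objective has no matching test

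*Protocol article*

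**What the plan says.** All references are to the Protocol article.

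- **Study design** opens with "A controlled randomized three-armed clinical trial was conducted". It then defines two groups: "The groups were differentiated based on whether or not they received Push notifications from a mobile application". It adds that "inside each group, three different subgroups were randomly established with distinct degrees of physical activity (PA) intensity", the levels being light, moderate and intense (LPA, MPA, IPA).
- The **title** and the **Abstract (Methods)** also give three arms, and the **Discussion** repeats it: "The intervention was evaluated through a randomized three-armed clinical test".
- **Sample size calculation** works with two groups: "The primary outcome variable was fat mass loss after six months", a difference of 2, an SD of at most 3.5 and 27 women per group. This is then raised for dropout: "A total of 90 women (45 for each group), was estimated". Activity level is not mentioned.
- **Statistical analysis** lists these methods: "For the bivariant hypothesis contrast, the two-means Student-t test was made"; a repeated-measures ANOVA at baseline, 3 and 6 months; an ANCOVA for the effect of baseline data; correlations; and adjusted linear regressions for the PUSH coefficient, whose adjustment variables are not given.
- The **Discussion** gives as its second objective that the study "analyzed the evolution of body composition based on PUSH notifications and prescribed physical activity".

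**The concern.** The label and the allocation cannot both be right. A reader who sees three arms may take the main contrast to be light versus moderate versus intense activity. The sample size and the first objective make it PUSH versus control.

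Activity level is also a randomised intervention, not an incidental covariate. According to the Physical activity section, two of the three levels receive exercise instructions and the third receives none, so the levels may well differ in fat loss. If they do, a PUSH comparison without that factor leaves the difference between levels in its error term. The second objective needs both factors in one model, and no listed analysis is tied to that. Left as it is, the choice of comparison and model stays open until results are seen.

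**Working it through.** **1. Counting the cells.** PUSH has 2 levels and activity has 3 inside each, so 2 × 3 = 6 cells. With equal allocation to activity levels (an assumption), 90/6 = 15 women per cell as enrolled, and 54/6 = 9 at the planning figure of 27 per group.

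**2. The plan's own figure.** Inputs: difference 2 and SD 3.5 (read as percentage points), power 80%, and two-sided alpha 0.05. That alpha is the level in Statistical analysis, with two-sidedness assumed; the sample size section prints 0.5. For two groups:

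n = 2 × (1.960 + 0.842)² × 3.5² / 2² = 48.1, i.e. 49 per group.

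The stated 27 is not reproduced. It matches a one-sample or paired t test (26.02, rounded up). That is a separate matter. What counts here is that the calculation has two groups and no activity factor.

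**3. Listed analyses against the two factors.**

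| Analysis | PUSH | Activity level | PUSH by activity |
|---|---|---|---|
| Two-means t test | possible | no | no |
| Repeated-measures ANOVA | between-woman factors not named | not named | not named |
| ANCOVA | not named | not named | not named |
| Adjusted regressions | yes | covariates not named | not named |

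**4. Variance left in the error term.** The documents give no activity effect, so take equal steps of x points between levels. The between-level variance is (2/3)x². If 3.5 is the SD within a cell:

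- x = 1: √(12.25 + 0.67) = 3.59, variance up 5.4%
- x = 2: √(12.25 + 2.67) = 3.86, variance up 22%
- x = 3: √(12.25 + 6.00) = 4.27, variance up 49%

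**5. Power for a 2-point PUSH effect**, by simulation (40,000 runs, balanced cells), t test without activity / model with activity:

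| Step x | 45 per group, 3.5 within-cell | 45 per group, 3.5 total | 27 per group, 3.5 within-cell |
|---|---|---|---|
| 0 | 76/76% | 77/77% | 54/54% |
| 1 | 75/77% | 77/78% | 52/54% |
| 2 | 70/77% | 79/86% | 46/54% |
| 3 | 61/76% | 84/96% | 36/53% |

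In balanced cells the true variance of the PUSH estimate contains only within-cell variation, while the t test's standard error contains more. The test is therefore conservative: with 3.5 within-cell and 45 per group, its simulated type I error is about 4.4%, 3.1% and 1.7% at x = 1, 2 and 3.

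**6. The joint objective.** Take a 2-point difference in PUSH effect between two activity levels, with SE = 3.5 × √(4/n) for n per cell and power Φ(2/SE − 1.96):

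- n = 15: SE = 1.81, power 20%, 95% CI half-width 1.99 × 1.81 = 3.6, detectable at 80% power 2.80 × 1.81 = 5.1 points
- n = 9: SE = 2.33, power 14%, half-width 2.01 × 2.33 = 4.7, detectable 6.5 points

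These figures assume 3.5 within-cell, and do not depend on the size of the activity effect.

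**The case against.** The strongest reply is that this is a condensed article. The adjusted regressions for PUSH may well include activity level, and a covariate list is commonly left to the full plan. Sizing a factorial trial on one main effect is legitimate, and the second objective does not claim a powered interaction. All of this stands, and it limits the point.

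Three stronger readings are tempting, and the documents do not support them.

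- A reader might infer that the PUSH analysis ignores activity. That is clear only for the t test, which is never named as the primary PUSH analysis.
- A reader might take the analysis for three or more means to be a comparison of activity levels pooled over PUSH. The text ties it to three time points and names no activity comparison.
- A reader might conclude that the error variance is inflated, or the PUSH result biased. Inflation depends on an activity effect that the article does not quantify. The loss of power against plan also depends on the SD being within-cell, which the article does not say. Under balanced allocation the estimate is unbiased and the test errs on the cautious side.

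The condensed format does not explain the rest. The three-armed label is a wrong statement about the design, not an omitted detail. The unmatched objective concerns a factor that the trial itself randomises, which is more than an unlisted covariate.

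**Conclusion.** The point holds in this form: the allocation described is a 2 × 3 factorial, the three-armed label contradicts it, and no analysis in the article is matched to the objective that involves both factors.

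The effect on the PUSH comparison is a possible loss of precision, not a loss of validity. At 45 per group it ranges from nothing, through about 2 power points at 1 point per activity step and 7 at 2, to about 15 at 3, if the SD of 3.5 is within-cell. If 3.5 is the total SD, nothing is lost against plan, but adjustment would still gain power, for example 79% to 86% at 2 points per step. The PUSH-by-activity contrast is weak in any case, at about 20% power with 15 per cell and 14% with 9.

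The assumptions are equal allocation to activity levels, equally spaced activity effects of 0 to 3 points, and two-sided alpha of 0.05. The wording and the model should be corrected, but the defect does not undermine the primary comparison.

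**What to change.** - Describe the trial as a 2 × 3 factorial with six cells, and replace the three-armed label in the title, Abstract, Study design and Discussion.
- State that the sample size is for the PUSH main effect, and whether the SD of 3.5 is within or across activity levels.
- Make the primary analysis the PUSH main effect from a linear model with PUSH, randomised activity level and the baseline value of the outcome.
- For the second objective, add the PUSH-by-activity term as exploratory, report it with confidence intervals, and say that it is not powered.

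The cost is wording and a few model terms, using data already collected. The activity factor takes 2 degrees of freedom from the primary model, which is negligible at either 54 or 90 women.

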### Sample size calculation

The primary outcome variable was fat mass loss after six months, and the anticipated minimum difference in the average fat mass loss was 2%, with an expected SD not exceeding 3.5% [35]. The study was designed to have at least an 80% power and an alpha level set at 0.5, obtaining a sample size of 27 individuals for each group (total *N* = 54). A total of 90 women (45 for each group), was estimated, to mitigate the effect of possible dropouts during this trial.

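### The stated 27 women per group do not give 80% power for the two-group comparison: power at the 5% level is about 54% with 27 per group and 76% with 45, and the alpha is printed as 0.5

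*Protocol article*

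**What the plan says.** The Sample size calculation section names the outcome: "The primary outcome variable was fat mass loss after six months". Its inputs are "the anticipated minimum difference in the average fat mass loss was 2%, with an expected SD not exceeding 3.5" (both in per cent). From these it claims that the study would "have at least an 80% power and an alpha level set at 0.5, obtaining a sample size of 27 individuals for each group", 54 in total. It then raises enrolment to 90, or 45 per group, as cover for dropouts, without giving a dropout rate.

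The Study design section describes the comparison as women who receive notifications against women who do not, so the two groups are independent. The Statistical analysis section names a two-means Student t test for comparing means and accepts "an alpha error probability of under 5" per cent, with 95% confidence intervals. No section mentions a one-sided test, pairing, or a baseline correlation as part of the sample size calculation.

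**The concern.** A standardised difference of 2/3.5 is a little over half an SD. Detecting that between two independent groups with 80% power usually takes about 50 per group, so 27 looked too small by nearly half. The alpha of 0.5 printed in the same sentence also conflicts with the level used for analysis.

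This paragraph is the only justification of the trial's size. It treats 27 evaluable women per group as enough and the remaining 18 per group as spare. If that is wrong, the stated power is a property the design does not have. Dropout down to the supposedly sufficient number would leave nearly an even chance of missing the effect the trial was built to find, and a non-significant result would say little against PUSH notifications.

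**Working it through.** **Inputs.** Difference 2, SD 3.5 and power 80% come from the Sample size calculation section. Two independent groups come from Study design. The two-means t test and the 5% level come from Statistical analysis. Sidedness is not stated. Two-sided is assumed, in line with the 95% intervals, and one-sided is also tried.

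Standardised difference: d = 2/3.5 = 0.571, so d² = 0.3265.

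**Trying to reproduce 27.** The exact results use the noncentral t distribution.

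| Reading | n for 80% power |
|---|---|
| Two-sample, two-sided 0.05 | 49.05, so 50 per group |
| Two-sample, one-sided 0.05 | 38.6, so 39 per group |
| Two-sample, two-sided 0.5 as printed | 13.2, so 14 per group |
| Two-sample, one-sided 0.5 | 4.3, so 5 per group |
| One-sample or paired, two-sided 0.05 | 26.02, so 27 in total |

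The normal formula agrees for the first row: 2 × (1.960 + 0.842)² / d² = 2 × 7.849 / 0.3265 = 48.07, so 49 per group.

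Only the last row gives 27 (power 81.5% at n = 27). That design tests a within-person change in one sample, and 27 is then the whole sample, not the size of each of two groups.

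**Power of the two-sample t test, two-sided 0.05, difference 2, SD 3.5**

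| Evaluable per group | Situation | Power |
|---|---|---|
| 27 | the number called sufficient (40% dropout from 45, since 1 − 27/45 = 0.40) | 54.0% |
| 36 | 20% dropout from 45 | 66.7% |
| 45 | no dropout | 76.5% |
| 50 | number needed | 80.8% |

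The normal approximation gives 55.6% at 27 and 77.4% at 45, so the conclusion does not depend on the method.

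**Detectable difference at 80% power:** 2.72 points with 27 per group and 2.09 with 45.

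**SD that would make 27 enough:** about 2.6. The normal formula gives 2 / [√(2/27) × 2.802] = 2.62, and the t test gives 2.57. The plan allows for 3.5.

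**The printed alpha.** Taken literally, "an alpha level set at 0.5" would give 27 per group about 92% power, so it explains neither the 27 nor the 80%. It is a second, separate error. The low power above follows from the 5% level in Statistical analysis, not from the 0.5.

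**The case against.** The strongest reply concerns the 45 per group to be enrolled, not the 27. Three unstated choices could bring 45 up to 80%:

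- **SD.** The 3.5 is given as a ceiling. An SD of about 3.35 gives 80% at 45 per group.
- **Sidedness.** It is not stated, and the hypothesis in the Background is directional. One-sided 0.05 gives 85% at 45.
- **Baseline adjustment.** Statistical analysis lists ANCOVA and adjusted regressions. If baseline correlates 0.3 with the outcome (an assumption; none is given), the variance falls by the factor 1 − 0.3² and power at 45 is about 80%. With a correlation of 0.5 it is 87%.

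This much stands: with no dropout the shortfall at 45 is modest, and 54% is the power at the number the plan calls sufficient, not a forecast. A confidence interval that excluded a 2-point benefit would also still be informative. That 27 came from a paired formula is an inference from an exact numerical match. Baseline adjustment with a correlation of about 0.66 (normal formula) would also give 27.

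None of this supports the text as printed. At 27 per group, one-sided testing gives 67% and a correlation of 0.5 gives 66%. The section states no correlation and no one-sided test, and the 95% intervals point to two-sided testing. A claim of at least 80% power has to hold at the planning SD of 3.5. The extra 18 women per group are there to be lost, so 45 evaluable per group is the best case.

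**Conclusion.** The concern holds. On the plan's own difference, SD and power, and the t test at 5% named for analysis, 27 per group is not the required size. The answer is 50 (49 by the normal formula), so 27 is little more than half of what is needed. Power is 54% at 27, 67% at 36 and 76% at 45 per group.

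These figures assume two-sided testing, SD 3.5 and an unadjusted comparison. Relaxing one of these in the trial's favour can lift 45 per group to 80% or more, but 27 falls short unless the SD is about 2.6 or the baseline correlation about two thirds, and the plan states neither. The alpha of 0.5 contradicts the 5% used elsewhere and is probably a misprint for 0.05. It needs correcting in its own right.

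**What to change.** Rewrite the Sample size calculation paragraph:

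1. Give alpha as 0.05, two-sided, in agreement with Statistical analysis.
2. Remove the statement that 27 per group (54 in total) gives 80% power. State that a two-sample comparison with difference 2 and SD 3.5 needs 50 evaluable women per group by the t test (49 by the normal formula).
3. State what the planned size delivers: 76% power and a detectable difference of 2.1 points with 45 per group and no dropout; 54% power and 2.7 points if only 27 per group are evaluable.
4. If a baseline-adjusted analysis is made primary, restate power for that analysis with the assumed correlation between baseline and week 24.

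The cost is one paragraph and a less favourable power statement. This correction requires no additional enrolment. It reports the power the trial has and does not restore the 80%.
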